**Trial registration number:**

I
SRCTN14077107 (ISRCTN registry dated on 3 March 2017).

Strengths and limitations of this studyThis sleep intervention consists of a brief behavioural intervention thus increasing the chances of the intervention being translated into clinical practice.This study is the largest randomised controlled trial to date on the efficacy of the Sleeping Sound program for children with autism spectrum disorder (ASD).Limitations of the study include: lack of an objective sleep measure, inability to control families’ use of additional sleep treatments post-trial enrolment and lack of gold standard ASD diagnostic tools (eg, Autism Diagnostic Observation Schedule—Second Edition, Autism Diagnostic Interview—Revised) to confirm ASD diagnosis.

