**Figure 2 F2:**
[figure not shown]
Flow of participants, figure format obtained from the CONSORT (Consolidated Standards of Reporting Trials) 2010 statement.^a^Complete teacher survey if applicable.

The TAU group will receive standard services and support currently available in the community and complete the same study assessment follow-up. If the parent consented to teacher participation, researchers approach schools for consent to contact the child’s teacher and then mail the teacher a baseline survey to complete.

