### Intervention group

*Delivery of the sleep intervention*. The behavioural sleep intervention is delivered by study-employed clinicians (paediatrician or psychologist experienced in working with children with ASD). Clinicians were trained over two × 3-hour interactive sessions (by HH and ES), have a detailed program manual and meet fortnightly to ensure fidelity to the program. The intervention consists of two 50 min face-to-face consultations and one follow-up phone call at 2-week intervals. The content of the original *Sleeping Sound* ADHD intervention^47^ has been adapted to children with ASD to include specific visual aids and social stories to assist in the delivery of the sleep intervention for this population.^56^ Intervention sessions are held in rooms at one of our study sites (Deakin University or The Royal Children’s Hospital) or the treating paediatrician’s consulting rooms, based on family preference.

The behavioural sleep interventions are individually tailored for the child and the family. The strategies that suit the family situation and learning style of the child with ASD are given emphasis. Delayed sleep phase, early morning waking and prolonged night waking (eg, waking overnight where the child is unable to fall back to sleep for an hour or more) are treated with bedtime fading (ie, the child’s bedtime is temporarily set later and gradually brought forward), as well as early morning light exposure. Need for parental presence at sleep time is managed for sleep-onset association using a ‘camping out’ method. Camping out involves parents gradually withdrawing themselves from the child’s bedroom over a period of time. Parent management strategies are used for bedtime resistance and can include use of a ‘bedtime pass’, whereby the child can only leave the bedroom once before sleep and may be coupled with a reward system. Primary insomnia (insomnia with no other established cause) is managed using relaxation training and restricting time in bed (ie, bedtime fading or getting out of bed and doing a relaxing activity if the child cannot fall asleep). In addition to relaxation training, examples of some strategies used to manage anxiety-related insomnia include discussing fears during the day rather than just before bedtime, encouraging the child to stay in bed and rewarding brave behaviour. Visual strategies, such as social scripts and visual timetables, are used to reinforce learning.

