*Session One* focuses on an assessment of the child’s sleep problems, psychoeducation about normal sleep and sleep cycles, good sleep habits, and a tailored sleep management plan specific to the sleep diagnosis of the child. As the Sleeping Sound intervention is individually tailored to children and families, participants are encouraged to provide input in relation to goal setting and the interventions they would like to try to assist in managing the sleep problems. Families receive written handouts, summarising session content and complete a written management plan with the clinician. A standardised consultation record is kept for all children including the presenting sleep problem(s), possible contributors to the problem (eg, TV in bedroom), medication use, comorbidities and bedtime routines. Clinicians record the duration of each consultation, sleep problem diagnoses, family sleep management goals, handouts given to parents and management options selected. Sleep problem diagnoses made may include one or more difficulties getting to sleep (sleep anxiety, bedtime resistance, sleep association onset disorder, delayed sleep phase or insomnia) and/or night waking problems (prolonged night waking or early morning waking). Parasomnias (nightmares, night terrors, sleep walking) are recorded, and psychoeducation and general management advice about parasomnias is provided, although these are not a focus of behavioural intervention.

*Session Two* is held 2 weeks later to review the sleep management plan (which includes a sleep diary), reinforce strategies, troubleshoot and monitor progress.

A *follow-up phone call* is conducted 2 weeks after the second visit to answer any further parent questions, reinforce strategies, troubleshoot and monitor progress.

Participants are able to withdraw from the intervention at any time. Participants are asked for feedback of the intervention at all intervention sessions, including follow-up, and this is documented by clinicians to manage any unintended adverse effects of the trial.

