### Sample size

In our pilot study,^48^ we found a moderate to large effect of the intervention on sleep for total CSHQ score (standardised mean difference=0.7). However, since effect sizes from small studies may not be replicated in larger studies, we conservatively estimate a moderate standardised mean difference of 0.5 at 3-month and 6-month follow-up. Required sample size for this standardised mean difference was calculated using the equation n=2 (Zα+Z [1−β])^2^×SD^2^/d^2^, where Z_α_ was set at p<0.05 (two tailed), Z_1−β_ (power) was set at 0.80, d was set at 0.5 as per above and the SD for this standardised mean difference was set at 1. The resulting sample size estimate was then adjusted for the impacts of attrition (allowing for 20% loss to follow-up) and clustering (by individual and paediatrician). Clustering was handled with adjustments for design effect, assuming intraclass correlation (ICC)=0.08 for the within-child’s paediatrician clustering (average cluster size=4, SD=3) and ICC=0.20 for the within-person clustering to control for repeated measurement due to control of baseline scores (estimated based on unpublished pilot data).^58^ Allowing for 20% attrition over time and these forms of clustering, we will randomise a minimum of 234 children (117 in each group) to ensure sufficient power postintervention with our primary outcome time point at 3 months post-randomisation. Full calculations are available in the online supplementary file.

10.1136/bmjopen-2019-029767.supp2Supplementary data

Strategies have been put in place to encourage participant retention and the completion of the follow-ups. These include a four-step reminder process for completing follow-up assessments and a study newsletter to promote family engagement.

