### Data analysis

Primary analysis will be intention-to-treat (within participant data included as per initial treatment group allocation, regardless of actual intervention received) and will compare outcomes of children in the TAU and intervention groups at the 3- and 6-month post-randomisation time points, though our primary endpoint is 3 months post-randomisation. Analysis of the primary outcome (ie, child sleep problems) and all secondary outcomes (child—teacher reported daytime sleepiness, sleep hygiene, emotional and behavioural problems, social communicative symptoms, cognitive performance, academic achievement, school attendance and quality of life; parent—parenting stress, mental health, quality of life and work attendance) will be carried out using linear mixed effects regression with results presented as mean differences (and 95% CIs). For each outcome, a single mixed-effects model will be fitted incorporating baseline, 3-month and 6-month data using random effects to allow for the repeated measures within an individual, and clustering of individuals within the child’s paediatrician. Separate parameters will be estimated for group differences at 3-month and 6-month postintervention; scores at baseline are added as a covariate. Differences in the outcomes of intervention and TAU groups will be assessed with linear mixed models, with individuals clustered within the child’s paediatrician and assessment times clustered within individuals. We will run an unadjusted model and compare this to an adjusted model, with the unadjusted model as our primary analysis, and adjusted results to evaluate robustness of these findings. The adjusted model will include the following as covariates: child gender, age, ASD symptom severity (measured using the Social Communications Questionnaire—current form,^53^ medication use (obtained from the Resource Use Questionnaire) and SES (measured according to the families residential postal code and using the index of relative socioeconomic disadvantage).^47 59^ The child’s paediatrician and individual participant will be modelled as random effects and the remaining variables will be handled as fixed effects. To account for missing data, the mixed models will be fitted using conditional maximum likelihood. As this approach makes an untestable assumption that data are missing at random, we will perform sensitivity analyses in the form of pattern mixture models to explore the effect of departure from this assumption. A per-protocol analysis will also be undertaken as a supplementary analysis. Significance will be tested at p<0.05 for the primary analysis, but adjustments for type I error inflation will be made for secondary outcomes by using the false discovery rate method.^60^

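### Excluding non-attenders from the supplementary per-protocol analysis would lose the protection of randomisation, because only the intervention arm has sessions to miss; a complier-average analysis should be added

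*Protocol article*

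**What the plan says.** Under Data analysis, the primary analysis is by intention to treat, with "data included as per initial treatment group allocation, regardless of actual intervention received". The same paragraph adds one sentence on a further analysis: "A per-protocol analysis will also be undertaken as a supplementary analysis". The article does not say who belongs to the per-protocol set.

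Under Intervention group, the programme is described: "The intervention consists of two 50 min face-to-face consultations and one follow-up phone call at 2-week intervals". It is delivered by clinicians employed by the study. On stopping, the text says "Participants are able to withdraw from the intervention at any time". On records, it says "Clinicians record the duration of each consultation, sleep problem diagnoses, family sleep management goals, handouts given to parents and management options selected".

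For the other arm, the text after Figure 2 says "The TAU group will receive standard services and support currently available in the community and complete the same study assessment follow-up". That arm has no study sessions.

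**The concern.** Adherence to the programme exists in one arm only. If the per-protocol set leaves out families who did not attend, those families go from the intervention arm. Their counterparts in TAU, who would not have attended had they been offered the sessions, cannot be identified and stay in. The groups then differ in composition as well as in treatment.

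Attendance could plausibly be related to outcome here. The Background links child sleep problems with parental stress, parent mental health and the home environment, and these could also affect whether a family comes to sessions. The primary outcome is reported by parents, who know their allocation and who also decide whether to attend.

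What is at stake is the interpretation of a supplementary result. Readers may take it as the effect of receiving the programme, when part of it could reflect which families attend.

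**Working it through.** **Plan's own figure.** From the Sample size section: standardised difference 0.5, SD 1, two-sided alpha 0.05, power 0.80, paediatrician ICC 0.08 with mean cluster size 4, within-person ICC 0.20, and 20% loss.

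- Base: 2(1.960 + 0.842)² / 0.5² = 62.79 per arm.
- Design effects: 1 + 3 × 0.08 = 1.24, and 1 + 1 × 0.20 = 1.20.
- 62.79 × 1.24 × 1.20 / 0.80 = 116.8, so 117 per arm and 234 in total. The stated figure reproduces and does not depend on the per-protocol question.
- Followed up: 117 × 0.80 = 93.6, taken as 94 per arm.

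**Bias when exclusion is for non-attendance only.** Express the effect as benefit, that is, reduction in the Children's Sleep Habits Questionnaire (CSHQ) score in SD units. Let c be the share who attend, τ the effect in attenders, and D the amount by which non-attenders' outcome without the programme is worse than attenders'. Assume that non-attenders gain nothing and that no TAU family receives the programme.

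- ITT estimate: cτ.
- Per-protocol estimate: τ + (1 − c)D, so its bias is (1 − c)D.
- CACE estimate: ITT / c = τ.

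**Numbers.** The documents give neither c nor D. Assumed ranges are c = 0.7 to 0.9 and D = -0.3 to +0.5, with τ = 0.50. The last column is the simulated two-sided rejection rate of the per-protocol comparison when τ = 0 (94 per arm, 5,000 replications, no baseline adjustment, no clustering).

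| c | D | ITT | Per-protocol | Bias | CACE | Rejection at τ = 0 |
|---|---|---|---|---|---|---|
| 0.9 | -0.3 | 0.45 | 0.47 | -0.03 | 0.50 | 0.054 |
| 0.9 | 0 | 0.45 | 0.50 | 0 | 0.50 | 0.052 |
| 0.9 | +0.3 | 0.45 | 0.53 | +0.03 | 0.50 | 0.054 |
| 0.9 | +0.5 | 0.45 | 0.55 | +0.05 | 0.50 | 0.062 |
| 0.8 | -0.3 | 0.40 | 0.44 | -0.06 | 0.50 | 0.071 |
| 0.8 | 0 | 0.40 | 0.50 | 0 | 0.50 | 0.051 |
| 0.8 | +0.3 | 0.40 | 0.56 | +0.06 | 0.50 | 0.063 |
| 0.8 | +0.5 | 0.40 | 0.60 | +0.10 | 0.50 | 0.097 |
| 0.7 | -0.3 | 0.35 | 0.41 | -0.09 | 0.50 | 0.082 |
| 0.7 | 0 | 0.35 | 0.50 | 0 | 0.50 | 0.049 |
| 0.7 | +0.3 | 0.35 | 0.59 | +0.09 | 0.50 | 0.080 |
| 0.7 | +0.5 | 0.35 | 0.65 | +0.15 | 0.50 | 0.147 |

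Simulation error is about √(0.05 × 0.95 / 5,000) = 0.003, so small differences between rows with the same absolute bias are noise.

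**Choice of exposure threshold.** CACE equals τ only if families below the threshold gain nothing. Suppose instead that 20% fall below a high threshold but gain half the effect, 0.25 SD. ITT is then 0.8 × 0.50 + 0.2 × 0.25 = 0.45, and CACE is 0.45 / 0.8 = 0.56 against a true 0.50. With a gap of 0.4 SD, per-protocol gives 0.50 + 0.2 × 0.4 = 0.58, so CACE loses most of its advantage. If the exposure is attendance at any session and those families each came once, they count as exposed. CACE is then 0.45 / 1 = 0.45, the average effect in families who started.

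**Precision at c = 0.8, SD 1.** The CACE standard error is about √(2/94) / 0.8 = 0.146 / 0.8 = 0.182. The per-protocol standard error, with 75 attenders, is √(1/94 + 1/75) = 0.155.

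**The case against.** A per-protocol analysis beside a primary ITT analysis is conventional, and nothing in the article contradicts it. Several stronger readings are tempting, and the documents do not support them.

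- *The per-protocol set loses families from one arm only.* The set is undefined here. It could also exclude for eligibility breaches or for "additional sleep treatments post-trial enrolment", which the article says it cannot control, and either could remove TAU families. One-sidedness holds for attendance-based exclusion only. Exclusions in TAU on other grounds would not restore the balance lost through attendance.
- *The definition of the set is missing.* An article commonly leaves this to the full protocol or statistical analysis plan, so it is no finding.
- *The analysis will overstate the effect.* That needs non-attenders to have the worse outlook. The later contacts review progress and troubleshoot, so a family whose child has improved might stop early, and the bias would then reverse. If D is zero there is no bias.
- *This is the only planned analysis of receiving the programme.* It is the only one in the article; the analysis plan is not shown.

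The magnitudes also ignore adjustment. The primary model includes the baseline score, and the adjusted model adds SES, ASD symptom severity, medication use, age and gender. If either is carried over to the per-protocol analysis, which the article does not say, only the residual gap matters.

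The strongest objection concerns the remedy. Session One alone provides psychoeducation, handouts and a tailored plan, so a CACE analysis that counts only full completers as exposed would break its own assumption. This stands, and it is why the exposure should be any session attended and why CACE should be added, with no case for outright replacement. Even then, parents who know their allocation report the outcome, which strains the exclusion restriction.

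**Conclusion.** The point holds in a limited form. Any exclusion for non-attendance would make the per-protocol result a comparison of selected intervention families with all TAU families, outside the protection of randomisation. Under the assumed 10-30% non-attendance and a gap of -0.3 to +0.5 SD, the bias runs from about -0.09 to +0.15 SD before baseline adjustment. The upper end is 0.15 / 0.5 = 30% of the design effect. The sign is unknown. With no true effect, the simulated rejection rate is near 5% when D is zero and reaches 0.147 at the worst corner.

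The inputs are assumptions, because the documents give no attendance rate and no prognosis gap. The consequence is modest: the analysis is labelled supplementary, and the primary ITT test and the sample size of 234 are untouched.

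**What to change.** Keep ITT primary. Add a supplementary CACE analysis of the primary outcome (CSHQ total at 3 months) that keeps every randomised family. Use allocation as the instrument and attendance at any intervention session, taken from the consultation records, as the exposure. Fix that threshold before the analysis. State the target plainly as the effect in families who would attend at least one session if offered the programme, and state the exclusion restriction: allocation affects the outcome only through attendance. Carry over the baseline score as a covariate and the allowance for clustering. If a per-protocol result is reported, label it a non-randomised comparison.

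The cost is a few sentences and one extra model on data already recorded. The interval is somewhat wider (standard error about 0.18 against 0.15 SD at 80% attendance, before clustering and adjustment), and the estimate rests on the exclusion restriction, which cannot be fully tested. Study clinicians deliver the programme and the article describes no route to it for TAU families, so one-sided non-compliance is a reasonable working assumption.

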### Economic evaluation

An important secondary aim of the project will be to determine the cost-effectiveness of this intervention compared with TAU. The inclusion of the Child Health Utility 9D at baseline, 3-month and 6-month follow-up will allow calculation of QALYs as part of a cost–utility analysis, applying the area-under-the-curve approach.^62^ A supplementary cost-effectiveness analysis will also be undertaken using the total CSHQ score as an outcome measure. The economic analysis will be conducted from a societal perspective, since interventions targeting children with ASD are likely to have benefits and costs beyond the narrow health sector (eg, ASD intervention services and productivity impacts for parents). A secondary analysis from a healthcare perspective will also be undertaken. The evaluation will first measure and value the use of healthcare resources over the period of the study between the two arms of the trial and then compare any additional costs to the additional outcomes achieved. Costs of the intervention will be measured using the financial records of the study team. Other costs incurred by children and their families will be measured using a Resource Use Questionnaire. Components of the Resource Use Questionnaire comprise the child’s use of healthcare services, including: (1) inpatient services and emergency services, (2) health professional visits, (3) medication and (4) other resources used. The questionnaire also collects data on out-of-pocket and travel costs, as well as on a child’s school attendance and parent’s productivity. Participants will also be asked for their permission to access their MBS and PBS data for a time period of 3 months prior to baseline up until the last follow-up assessment. These data are not subject to recall bias and provide complete resource use costs (and out-of-pocket costs) for all MBS and PBS reimbursed healthcare services. Non-MBS and non-PBS funded services (eg, state-funded ASD services) will be captured in the Resource Use Questionnaire. Generalised linear models will be used to assess mean difference in costs and outcomes between the two arms, adjusted for any differences between groups at baseline. An incremental cost-effectiveness ratio and an incremental cost–utility ratio will be calculated as the difference in average cost between the groups, divided by the difference in average CSHQ and QALYs, respectively. Non-parametric bootstrapping will be undertaken from the observed cost/QALY pairs (1000 simulated replications) to determine CIs and presented in a cost-effectiveness plane along with a cost-effectiveness acceptability curve. Sensitivity analyses will be carried out to explore the robustness of the results. While MBS and PBS data will be used for the base case analysis, a sensitivity analysis will be performed using self-report data derived from the Resource Use Questionnaire for those health services not captured by MBS and PBS.

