**E** **CONOMIC** **OUTCOMES**					
Resource use	Family reported **service use** over preceding 3 months.	Parent	●	●	●
Health service utilisation	Permission to access both **Medicare and Pharmaceutical Benefits Scheme (PBS**) data for 3 months prior to baseline up until the last follow-up assessment.	Linkage	●	●	●

●Measure used at indicated time point.

3, 3 months; 6, 6 months; ASD, autism spectrum disorder; B, baseline; NIH, National Institutes of Health.

We have chosen the CSHQ as our primary outcome measure as this is a widely used and validated measure of behavioural sleep problems in children,^49^ and was used in our pilot *Sleeping Sound* ADHD-ASD study.^48^ It has been used to examine sleep behaviour in children with ASD and correlates highly with the objective measure of actigraphy.^57^ It contains 33 items and includes 8 subscales: Bedtime Resistance (eg, *Child falls asleep in own bed*), Sleep-Onset Delay (eg, *Child falls asleep in 20 min after going to bed*), Sleep Duration (eg, *Child sleeps the right amount*), Sleep Anxiety (eg, *Child needs parent in the room to fall asleep*), Night Waking (eg, *Child moves to someone else’s bed during the night*), Parasomnias (eg, *Child talks during sleep*), Sleep Disordered Breathing (eg, *Child snores loudly*) and Daytime Sleepiness (eg, *Child has difficulty getting out of bed in the morning*). A 3-point rating scale from 1=*rarely* to *3*=*usually* is applied to each item, indicating the sleep problem frequency during the past week. Some items are reverse coded and higher scores are indicative of more sleep problems. The measure has good internal consistency (α=0.78) and each subscale also has adequate internal consistency (α=0.93–0.56).^49^

Knowledge of participant group status will be limited to the project coordinator and study clinicians. If a family spontaneously reveals their intervention status to another team member, this is noted on the participant file. Given that it is impossible to maintain participant blinding in a trial of this nature, we have carefully chosen some outcome measures that can be assessed in a blinded fashion. For example, we will include a blinded teacher-reported measure of sleep, behavioural, social and motor functioning. We will not inform teachers of the child’s group status and will ask parents not to inform teachers. We will also include blinded objective child measures of executive and school-based functioning.

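### The baseline adjustment planned for the economic models is open-ended and is not carried into the cost-effectiveness ratios or the bootstrap

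*Protocol article*

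**What the plan says.** Three consecutive statements in the Economic evaluation section of the protocol article describe the estimation.

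- Generalised linear models are to estimate the "mean difference in costs and outcomes between the two arms, adjusted for any differences between groups at baseline". No covariates are named.
- The cost-effectiveness and cost-utility ratios are "calculated as the difference in average cost between the groups, divided by the difference in average CSHQ and QALYs, respectively". The section does not say whether these averages are raw or model-adjusted, and gives no order of subtraction.
- For uncertainty: "Non-parametric bootstrapping will be undertaken from the observed cost/QALY pairs (1000 simulated replications". The resulting intervals are shown on a cost-effectiveness plane with an acceptability curve. The statistic to be computed in each replicate is not stated.

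QALYs come from CHU9D at baseline, 3 and 6 months, "applying the area-under-the-curve approach". On the CSHQ, used for a supplementary ratio, the Measures section says that "higher scores are indicative of more sleep problems".

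The Data analysis section handles the clinical outcomes differently. There the baseline score is always a covariate, and the further covariates of the adjusted model are listed by name.

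**The concern.** Two things are left loose. First, "adjusted for any differences between groups at baseline" can be read as choosing covariates after seeing which baseline variables differ. That makes the economic estimate depend on a data-driven choice that the clinical models avoid.

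Second, the adjustment appears only in the sentence on the models. A cost/QALY pair, taken literally, holds no separate baseline utility or baseline cost, so the adjusted models cannot be refitted from the pair alone. An analyst who follows the text could report adjusted mean differences beside an unadjusted ratio, interval, plane and acceptability curve. The two sets could point in different directions for the same trial. Child quality of life could likewise be baseline-adjusted as a secondary outcome and unadjusted in the cost-utility ratio. The article calls cost-effectiveness an important secondary aim and states a hypothesis about it.

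**Working it through.** The plan gives no figure on this point to reproduce. The check asks how far the incremental QALY can move if the adjustment is left out.

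**From the article:** CHU9D at 0, 3 and 6 months; 117 children per group (Sample size).

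**Assumed, since the article gives neither:** utility SD of 0.10 to 0.20, and a correlation *r* of 0.5 to 0.7 between any two visits.

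**Step 1: QALY weights.** With visits at 0, 0.25 and 0.5 years, the trapezoid rule gives

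QALY = 0.125 × baseline + 0.25 × month 3 + 0.125 × month 6.

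**Step 2: size of a chance imbalance.** The standard error of the baseline utility difference is SD × √(2/117). At SD 0.15 this is 0.15 × 0.1307 = 0.0196.

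**Step 3: shift in the unadjusted QALY difference.** A baseline imbalance enters directly (0.125) and through its correlation with follow-up (0.375 × *r*):

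shift = imbalance × (0.125 + 0.375 × *r*).

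At SD 0.15 and *r* = 0.5: 0.0196 × 0.3125 = 0.0061.

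**Step 4: precision.** The QALY variance is SD² × (0.09375 + 0.15625 × *r*). Adjusting for baseline removes SD² × (0.125 + 0.375 × *r*)². Multiplying by 2/117 and taking the square root gives the standard errors below.

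| SD | r | One-SE imbalance | Shift in QALY difference | SE, unadjusted | SE, adjusted |
|---|---|---|---|---|---|
| 0.10 | 0.5 | 0.0131 | 0.0041 | 0.0054 | 0.0036 |
| 0.10 | 0.7 | 0.0131 | 0.0051 | 0.0059 | 0.0030 |
| 0.15 | 0.5 | 0.0196 | 0.0061 | 0.0081 | 0.0053 |
| 0.15 | 0.7 | 0.0196 | 0.0076 | 0.0088 | 0.0045 |
| 0.20 | 0.5 | 0.0261 | 0.0082 | 0.0108 | 0.0071 |
| 0.20 | 0.7 | 0.0261 | 0.0101 | 0.0118 | 0.0060 |

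The adjusted standard error is about 66% of the unadjusted one at *r* = 0.5 (0.0036/0.0054) and about 51% at *r* = 0.7 (0.0030/0.0059). For scale, an assumed utility gain of 0.03 at both follow-ups is worth 0.03 × 0.375 = 0.01125 QALYs.

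**Step 5: simulation** (SD 0.15, *r* = 0.6, true difference 0.01125). Over 4,000 simulated trials both estimators centred on the truth (0.0114 each). Their standard deviations were 0.0086 unadjusted and 0.0050 adjusted. The unadjusted estimate correlated 0.81 with the baseline imbalance, the adjusted one 0.02.

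One further simulated trial had a baseline imbalance of −0.031, about 1.6 standard errors (0.031/0.0196). The adjusted model gave 0.0105. Over 1,000 bootstrap samples of whole records, refitting that model averaged 0.0104, while raw means in the same samples averaged −0.0006. The statistic computed in each replicate therefore decided the sign of the incremental QALY.

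**The case against.** The strongest reply is that the article never calls the differences raw. The sentence before the ratio definition describes adjusted differences, and a reader may carry them forward. Naming what is resampled does not fix what is computed in each replicate, and the simulation shows that resampling whole records with a refit reproduces the adjusted result. This stands in part: the text permits the right analysis, but it does not require it, and its literal wording fits the unadjusted one at least as well. Similarly, the phrase on baseline differences may only mean adjustment for baseline values.

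A second reply is that randomisation protects the unadjusted estimate from bias, and an unadjusted bootstrap would reflect its wider uncertainty. That stands. The loss is in precision and in agreement between the reported results.

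Two stronger readings are tempting but not supported.

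- A reader might infer that resampling observed pairs drops families with incomplete data. The article does not say so. The word may simply contrast with simulated replications, and rules for missing economic data may sit in an analysis plan that is not shown.
- A reader might infer that the CSHQ ratio has the wrong sign because a higher score is worse. No order of subtraction is given, so the sign is unspecified, not reversed. It concerns only the supplementary ratio and does not arise in the bootstrap sentence.

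**Conclusion.** The point holds as a gap in specification, not as proof that the ratios will be unadjusted. The covariate rule can be read as dependent on observed imbalance, and the adjustment is not carried into the ratios, intervals, plane or acceptability curve.

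If it is left out, a one-standard-error imbalance in baseline CHU9D moves the incremental QALY by about 0.004 to 0.010. The standard error is then 0.005 to 0.012, compared with 0.003 to 0.007 after adjustment. These sizes rest on the assumed SD and correlations and on 117 children per group with complete utilities. No size is given for costs, since the article offers no cost figures.

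The point affects a secondary analysis only and leaves the primary outcome untouched. It is worth correcting because the data needed are already being collected.

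**What to change.** In the economic analysis plan:

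1. Name the covariates in advance: baseline CHU9D in the QALY model and pre-baseline cost in the cost model, whatever imbalance is observed. Table 3 shows that both can be obtained: CHU9D and family-reported service use are collected at baseline, and linked Medicare and PBS data reach back 3 months before it.
2. Resample whole participant records within each arm, not bare cost/QALY pairs.
3. Refit the adjusted cost and QALY models in each replicate, and take the ratios, confidence intervals, plane and acceptability curve from those adjusted differences.
4. As a minor clarification, define the CSHQ denominator as points of reduction (TAU minus intervention). With invented figures, an extra cost of 500 and a 4-point improvement then reads as +125 per point (500/4); the opposite order gives −125.

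The cost is a few sentences of wording and slightly more computing. No new data are needed.
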